### Study Settings and Participants

All participants undergo standard medical treatment after surgery and are involved in the efficacy assessment of RYJHS external application. Figure 1 shows the study’s flowchart. Both groups apply a patch plaster on the back of the wrist without wounds (avoiding the suture of the fracture operation). Figure 2 shows the site of the medication application. The experiment group apply the RYJHS plaster, while the control group apply a placebo plaster. The patch is applied twice a day, for 6 hours each time, with a 6-hour break in between, repeated for 3 days, completing one course of treatment. Patients undergo two courses of treatment, with the first course completed during hospitalization, and the second course completed 3 days after discharge.

**Figure 1 figure1:**
[figure not shown]
CONSORT (Consolidated Standards of Reporting Trials) flow diagram of enrollment, randomization, treatment, and evaluation. CRP: C-reactive protein; DASI: Dyshidrotic Eczema Area and Severity Index; ORIF: open reduction and internal fixation; PRWE: Patient-Rated Wrist Evaluation; RYJHS: Ru-Yi-Jin-Huang-Saan.

**Figure 2 figure2:**
[figure not shown]
Applying Ru-Yi-Jin-Huang-Saan (RYJHS) plaster on Colles fracture after surgery. (A) The surgical incision site. (B) The site of the RYJHS plaster on a Colles fracture after surgery.

### Inclusion Criteria

To be eligible for our study, patients must meet the following criteria: be 20-80 years of age, have a Colles fracture (Frykman classification type I-VI) [59] diagnosis that has been treated with open reduction and internal fixation (ORIF) surgery, and provide informed consent either personally or through their family members.

### Exclusion Criteria

The following exclusion criteria will be applied: age older than 80 years or younger than 20 years; inability to comply with experimental procedures or complete questionnaires; presence of wounds on the back of the wrist; allergy to the herbal patch before; use of other Chinese herbal topical medicine after fracture; pregnancy; cancer; stroke; and systemic diseases such as severe anemia, thyroid disease, and poorly controlled diabetes.

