**Methods:**

This is a protocol for a randomized, double-blind, placebo-controlled trial. A total of 100 postoperative patients with Colles fracture, aged 20-80 years, will be recruited for this study. They will be randomly assigned to either the experimental or control group in a 1:1 allocation ratio. Both groups will receive standard postoperative Colles fracture treatment. The primary outcome measure will assess wrist functional recovery using the Patient-Rated Wrist Evaluation score. Secondary outcomes will include C-reactive protein levels and ultrasound measurements of wrist swelling. All of these examinations will be assessed at baseline, 3 days after surgery, and 6 days after surgery. In addition, the Dyshidrotic Eczema Area and Severity Index will be used to monitor for adverse skin reactions.

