## Methods

### Study Design

The study is a randomized, double-blind, placebo-controlled trial design based on SPIRIT (Standard Protocol Items: Recommendations for Interventional Trials) reporting guidelines (Multimedia Appendix 1) [57], and the results will follow the CONSORT (Consolidated Standards of Reporting Trials) guidelines [58]. Our research project is scheduled to recruit patients from May 1, 2023, to April 30, 2025. All postoperative patients with Colles fracture will be recruited through referrals from orthopedic physicians at Changhua Christian Hospital. Researchers will screen and select participants based on specific inclusion and exclusion criteria. In this study, all participants are randomly assigned using a computerized block randomization schedule. We randomly generate a pool of 100 patients, who are assigned to sequentially numbered opaque envelopes. The treatment allocations are balanced within each group, with each group containing 50 patients. Researchers and patients are both blinded to the treatment allocation, with the exception of the statistician responsible for the randomization process. The two groups in the study consisted of the experimental group receiving RYJHS treatment and the control group receiving a placebo.

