### Study Medication

RYJHS is a common TCM plaster that has been used for more than 500 years. RYJHS is composed of 10 herbs: *Trichosanthis radix*, *Rhei radix et rhizoma*, *Phellodendri cortex*, *Curcumae longae rhizoma*, *Angelicae dahuricae radix*, *Magnolite cortex*, *Glycyrrhizae radix et rhizoma*, *Citri reticulatae pericarpium vetum*, *Atractylodis rhizoma*, and *Arisaematis rhizoma* (given in Table 1). This herbal formula is a fixed prescription announced by the Department of Chinese Medicine and Pharmacy. The RYJHS used in our study is manufactured by Kaiser Pharmaceutical Co and meets the requirements of Good Manufacturing Practice. It has also been issued a drug certificate. The placebo powder, which uses computer color-matching technology in the color simulation of RYJHS [61], is also produced by Kaiser Pharmaceutical Co. Both RYJHS and the placebo are prepared by mixing 13 grams of powder with 23 mL of water, which is then evenly spread onto a cotton cloth and covered with gauze for later use. The aforementioned procedures are all carried out by the same experienced technician, as given in Figure 3.

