### Outcome Measurements

In this study, we will gather data from each participant including their gender, age, affected hand and dominant hand, Patient-Rated Wrist Evaluation (PRWE) score, C-reactive protein (CRP) levels, wrist ultrasound results, wrist x-ray images, and Dyshidrotic Eczema Area and Severity Index (DASI) score. Patients who have undergone Colles fracture surgery are required to be evaluated, and data will be collected before the trial, as well as 3 days and 6 days after topical medication application. The participant timetable of enrollment, assessments, and treatments is given in Table 2. The primary outcome is the PRWE score, which is used to assess wrist function recovery. The PRWE score, collected via a questionnaire, was developed in Canada for patients with wrist problems to express their pain and level of function [62]. The secondary outcomes are CRP level and wrist imaging records, which are used to demonstrate the degree of inflammation and swelling reduction. In addition, the DASI score is used to monitor any allergic or adverse events that may occur at the application site [63].

**Table 2 table2:** Timetable of enrollment and assessments.

Time			Screening		Baseline		Treatment 1 at hospital		Treatment 2 at home
			D_0_^a^		D_1_		D_3_		D_6_

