**Enrollment**									
	Inclusion or exclusion	✓		—^b^		—		—	
	Informed consent	✓		—		—		—	
	Demographic data	✓		—		—		—	
	Dominant and affected hand	—		✓		—		—	
	Medical history	✓		—		—		—	
	Randomization	—		✓		—		—	

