### Ethical Considerations

Approval for this trial (protocol ID 221006) was granted by the Institutional Review Board of Changhua Christian Hospital (CCH) on November 25, 2022, following the principles outlined in the Declaration of Helsinki. The study protocol has also been registered on ClinicalTrials.gov (NCT05638360). Individuals interested in participating will be required to provide written informed consent before the study’s initiation. They will receive comprehensive information about the study, including procedures, potential benefits, and risks, excluding specific details regarding the RYJHS medication. Participants are free to withdraw at any time without any impact on their future medical care.

Data collected will be anonymized to protect participants’ privacy, and all information will be kept confidential according to institutional data protection policies. No direct compensation will be provided to participants. The results of this research will be disseminated through publication in a peer-reviewed journal and presented at scientific conferences.

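### The only allergy exclusion requires a past reaction to a herbal patch, so a known allergy to one of the ten RYJHS ingredients does not make a patient ineligible under the written criteria

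*Protocol article*

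**What the plan says.** In the protocol article, Exclusion Criteria, the single allergy item is "allergy to the herbal patch before". The Inclusion Criteria cover age, fracture type treated by ORIF, and consent; they do not mention allergy. Study Design makes these lists the basis for selection: "Researchers will screen and select participants based on specific inclusion and exclusion criteria".

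Study Medication states that "RYJHS is composed of 10 herbs", and Table 1 names each with its proportion. Table 2 schedules "Medical history" at screening (D0), before randomisation at D1, with no allergy rule attached.

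Under Ethical Considerations, participants are told about procedures, benefits and risks, "excluding specific details regarding the RYJHS medication". For safety, Outcome Measurements says that "the DASI score is used to monitor any allergic or adverse events that may occur at the application site"; Table 2 places the DASI at baseline, D3 and D6, with adverse events recorded at any time.

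**The concern.** A patient can have reacted to turmeric, liquorice, tangerine peel or rhubarb without ever having worn a herbal patch. That history is known in advance and bears directly on a product made of these ingredients, yet the criterion as worded does not catch it. Two things are at stake. The first is an avoidable skin reaction in a patient who could have been identified beforehand. The second is the safety result: skin reaction at the application site is what the DASI is there to monitor, and reactions in patients with a known ingredient allergy would mix a gap in screening with the tolerability of the product in suitable patients.

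**Working it through.** The point is about wording, and the plan gives no figure of its own to reproduce. The relevant sections, taken in the order a patient meets them, are as follows.

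1. **Eligibility.** Take a patient aged 20 to 80 with a qualifying fracture, a known allergy to one Table 1 ingredient, and no earlier reaction to a patch. The patient meets the Inclusion Criteria. The allergy exclusion does not apply. The term for the patch is not defined: it could mean RYJHS or any herbal patch. Either reading requires a previous patch reaction, so neither captures this patient.
2. **Screening.** Medical history at D0 may bring the allergy to light. If it does, the written criteria give staff no ground to exclude.
3. **Consent.** Risks are disclosed, but specific details of RYJHS are left out. If those details include the ingredients, a patient has less reason to mention an allergy to one of them. The article does not say whether they do.
4. **Allocation.** Patients are "randomly assigned to either the experimental or control group in a 1:1 allocation ratio", so such a patient has a 50% chance of RYJHS. The placebo's composition is not given, so nothing can be said about the other 50%.
5. **After allocation.** The DASI and adverse event recording detect a reaction only once the plaster has been applied.

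The size can be bounded by simple arithmetic:

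- Maximum exposure, from Study Settings and Participants: 2 applications a day × 3 days × 2 courses = 12 applications; 12 × 6 hours = 72 hours. This is reached only if no application is missed or stopped.
- Effect on the RYJHS arm, with 50 patients per group (Study Design): one reacting patient = 1/50 = 2 percentage points in the proportion with any skin reaction. The article describes the DASI as a score and defines no such proportion, so this is only a gauge of scale.
- Number of such patients: not given. Purely as an assumption, 1 to 3 in the RYJHS arm, all reacting, would give 1/50 to 3/50, or 2 to 6 points. Under 1:1 allocation this corresponds to about 2 to 6 among the 100 enrolled. With none, or if none reacts, the shift is zero.

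**The case against.** The case against has four parts.

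- **Medical history is a real safeguard.** It is taken from every patient before randomisation, and a clinician who heard of a relevant allergy might well not enrol the patient. This stands, so a reader should not infer that such a patient is certain to pass screening in practice. It does not close the gap, because the written criteria do not call for exclusion.
- **Consent discloses risks and does not expressly withhold the ingredient list.** This also stands. A reader might infer that patients are kept ignorant of the ingredients and so have no prompt to disclose. The article does not go that far, and the consent form is not shown. The wording may make disclosure less likely, and no more can be claimed.
- **A journal article condenses the protocol, and fuller hypersensitivity wording may exist elsewhere.** That would answer a complaint about a missing topic. Here the allergy criterion is stated, and as stated it is too narrow for a product with ten ingredients.
- **The Introduction reports that RYJHS relieves inflammatory pain without sensitisation.** That concerns the product causing new sensitisation. It does not address patients who are already allergic, and the trial's own allergy exclusion and DASI monitoring treat reactions as possible.

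Two further inferences are tempting. One is that reactions would occur only in the RYJHS arm and unblind patients; without the placebo's composition this is not shown. The other is that naming the ingredients to every candidate could not affect blinding. Only colour matching of the placebo is described, so patients who know which herbs to expect might judge their plaster by smell, and the primary outcome, PRWE, is patient-reported.

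**Conclusion.** The point holds as a defect of wording. Under the written criteria, a known allergy to a RYJHS ingredient without an earlier patch reaction does not exclude a patient, and nothing in the stated screening acts on that allergy. The conclusion rests on the text of the eligibility, composition and screening sections; the consent sentence is only a contributing factor. The size is unknown and probably small: 2 percentage points in the RYJHS arm for each such patient who reacts, with 72 hours as the maximum contact. The documents give no count of such patients and do not support a claim that the safety result will be materially distorted. The change is worth making because it is cheap and concerns a foreseeable risk to patients.

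**What to change.** Reconcile the Exclusion Criteria with the composition in Table 1 and Study Medication, so that the allergy item also covers known hypersensitivity to components of the study plasters, both RYJHS and placebo. Ask every candidate about this as part of the medical history already scheduled at D0, before randomisation. Clarify under Ethical Considerations that the details left out of the participant information do not prevent this screening. The exact clinical wording is for the investigators to settle.

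The cost is one reworded criterion, one clarified consent sentence, the ethics board's handling of both, and a few possible screen failures. There is also a small possible effect on blinding if ingredients are named to patients; asking about allergies without describing the product limits it. The reach is limited to patients not yet randomised. The article appeared on March 5, 2025 and recruitment was planned to end on April 30, 2025, so few may remain. The article's latest enrolment count, 32 patients as of December 2023, does not show how many.

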### Sample Size Calculation

Our study closely resembles the design of phase-2 studies in clinical trials, which aim to assess the effectiveness of drugs in participants with specific conditions or diseases. We used G*Power (Heinrich-Heine-Universität Düsseldorf) to estimate the necessary sample size for our study, taking into account repeated-measures ANOVA within-between interactions with a medium effect size of f=0.25 and α level=.05. To achieve a statistical power of 0.95, we calculated a total sample size of 86 [60]. To account for potential dropouts and satisfy our inclusion criteria, we will enroll 100 individuals who have been admitted to our orthopedic care ward and diagnosed with Colles fracture after surgery.

### Study Medication

RYJHS is a common TCM plaster that has been used for more than 500 years. RYJHS is composed of 10 herbs: *Trichosanthis radix*, *Rhei radix et rhizoma*, *Phellodendri cortex*, *Curcumae longae rhizoma*, *Angelicae dahuricae radix*, *Magnolite cortex*, *Glycyrrhizae radix et rhizoma*, *Citri reticulatae pericarpium vetum*, *Atractylodis rhizoma*, and *Arisaematis rhizoma* (given in Table 1). This herbal formula is a fixed prescription announced by the Department of Chinese Medicine and Pharmacy. The RYJHS used in our study is manufactured by Kaiser Pharmaceutical Co and meets the requirements of Good Manufacturing Practice. It has also been issued a drug certificate. The placebo powder, which uses computer color-matching technology in the color simulation of RYJHS [61], is also produced by Kaiser Pharmaceutical Co. Both RYJHS and the placebo are prepared by mixing 13 grams of powder with 23 mL of water, which is then evenly spread onto a cotton cloth and covered with gauze for later use. The aforementioned procedures are all carried out by the same experienced technician, as given in Figure 3.

**Figure 3 figure3:**
[figure not shown]
Preparation of Ru-Yi-Jin-Huang-Saan (RYJHS) plaster. (A) Spread the paste onto a cotton cloth and (B) cover with gauze.

### Outcome Measurements

In this study, we will gather data from each participant including their gender, age, affected hand and dominant hand, Patient-Rated Wrist Evaluation (PRWE) score, C-reactive protein (CRP) levels, wrist ultrasound results, wrist x-ray images, and Dyshidrotic Eczema Area and Severity Index (DASI) score. Patients who have undergone Colles fracture surgery are required to be evaluated, and data will be collected before the trial, as well as 3 days and 6 days after topical medication application. The participant timetable of enrollment, assessments, and treatments is given in Table 2. The primary outcome is the PRWE score, which is used to assess wrist function recovery. The PRWE score, collected via a questionnaire, was developed in Canada for patients with wrist problems to express their pain and level of function [62]. The secondary outcomes are CRP level and wrist imaging records, which are used to demonstrate the degree of inflammation and swelling reduction. In addition, the DASI score is used to monitor any allergic or adverse events that may occur at the application site [63].

**Table 2 table2:** Timetable of enrollment and assessments.

Time			Screening		Baseline		Treatment 1 at hospital		Treatment 2 at home
			D_0_^a^		D_1_		D_3_		D_6_
**Enrollment**									
	Inclusion or exclusion	✓		—^b^		—		—	
	Informed consent	✓		—		—		—	
	Demographic data	✓		—		—		—	
	Dominant and affected hand	—		✓		—		—	
	Medical history	✓		—		—		—	
	Randomization	—		✓		—		—	
**Assessment**									
	PRWE^c^ score	—		✓		✓		✓	
	CRP^d^	—		✓		—		✓	
	Ultrasound	—		✓		✓		✓	
	X-ray	—		✓		—		✓	
	DASI^e^ score	—		✓		✓		✓	
	Adverse events	—		Record at any time^f^		Record at any time		Record at any time	

^a^D_x_: number of days into the experiment.

^b^Not available.

^c^PRWE: Patient-Rated Wrist Evaluation.

^d^CRP: C-reactive protein.

^e^DASI: Dyshidrotic Eczema Area and Severity Index.

^f^If a patient has any side effects during the experiment, they must be recorded immediately.

### Statistical Analysis

We will conduct statistical analyses using the SPSS software (version 22; IBM Corporation). Descriptive analyses will be performed on demographic data using frequencies and percentages to characterize the sample. Categorical variables will be compared using chi-square tests, while continuous variables will be compared using 2-tailed *t* tests. We will use repeated-measures ANOVA to determine if changes in wrist function (the dependent variable) are due to the interaction between the “type of treatment” (RYJHS) and “time” (measurement time). Multiple regression will be used to assess the impact of latent factors on primary outcomes (wrist function) and secondary outcomes (swelling and inflammation), adjusting for all possible covariates. Regression models will be performed in different outcome groups to compare the effects of different treatments (RYJHS intervention vs placebo).

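### The fixed test of wrist function, a group-by-time interaction, names no deciding visit and gives no treatment difference in PRWE at the end of the two courses

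*Protocol article*

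**What the plan says.** All references are to the Methods of the protocol article.

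- **Outcome Measurements:** "The primary outcome is the PRWE score, which is used to assess wrist function recovery". No visit, change score or summary is attached to it. On timing, "data will be collected before the trial, as well as 3 days and 6 days after topical medication application". Table 2 places PRWE at D1 (baseline, the same column as randomization), D3 and D6.
- **Statistical Analysis:** "We will use repeated-measures ANOVA to determine if changes in wrist function (the dependent variable) are due to the interaction between the" type of treatment and time, where time is glossed only as measurement time. The section also plans two-tailed *t* tests for continuous variables, a multiple regression for primary and secondary outcomes with adjustment for all possible covariates, and regression models comparing RYJHS with placebo. None of these names a visit or baseline PRWE.
- **Sample Size Calculation:** the trial is sized by "taking into account repeated-measures ANOVA within-between interactions with a medium effect size of f=0.25 and α level=.05". The result is given as "To achieve a statistical power of 0.95, we calculated a total sample size of 86", and then "To account for potential dropouts and satisfy our inclusion criteria, we will enroll 100 individuals". The number of measurements and the correlation between them are not given.

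**The concern.** The interaction is fixed in two places, as the test of wrist function and as the basis of the sample size. It is therefore a stated choice, not a detail left to a fuller document.

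PRWE on D1 is taken at randomization, so the arms share one true baseline mean. Repeated-measures ANOVA with three time levels treats that score as one more outcome and makes no use of this equality. The test then asks whether the two three-point profiles are non-parallel in any way. A significant result could come from a difference at D3, at D6 or at both. It carries no estimate of how much better PRWE is after two courses, which is what a reader of an efficacy trial wants to know. In many plausible situations it is also less likely to detect such a benefit than a baseline-adjusted comparison of the same data.

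**Working it through.** **1. The plan's own figure.** For a within-between interaction with k = 2 groups and m measurements:

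λ = f²·N·m/(1−ρ), df1 = (k−1)(m−1), df2 = (N−k)(m−1).

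From the protocol, f = 0.25 and α = 0.05. Assumed here: m = 3, ρ = 0, sphericity.

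- N = 84: λ = 0.0625 × 84 × 3 = 15.75, df 2 and 164, power 0.950.
- N = 86: λ = 16.125, df 2 and 168, power 0.955.
- With the multivariate denominator (df2 = N−3), 86 is the smallest N that reaches 0.95.

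So 86 is consistent with three time levels including baseline. It does not prove this, because m = 2 with ρ = 0.2 also gives 86. With m = 3 and ρ = 0.5 the formula gives 44.

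**2. What f = 0.25 means as a PRWE difference.** Let δ be the arm difference at each visit in SD units and S = Σ(δⱼ − mean δ)². Then λ = (N/4)·S/(1−ρ). Equating the two expressions for λ gives S = 4·m·f² = 4 × 3 × 0.0625 = 0.75.

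- Gradual effect (0, δ/2, δ): S = δ²/2, so δ = √1.5 = 1.22 SD at D6.
- Sustained effect (0, δ, δ): S = 2δ²/3, so δ = √1.125 = 1.06 SD at D6.

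**3. Power for a smaller effect.** Assumed: N = 86, 0.5 SD at D6, compound symmetry, no expected baseline difference. None of the effect size, its shape or the correlation is in the protocol.

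Worked at ρ = 0.5:

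- Gradual (0, 0.25, 0.5): S = 0.125, λ = 21.5 × 0.125/0.5 = 5.375, power 0.53.
- Sustained (0, 0.5, 0.5): S = 0.1667, λ = 21.5 × 0.1667/0.5 = 7.17, power 0.66.
- ANCOVA at D6: noncentrality δ/√(4(1−ρ²)/N) = 0.5/√(4 × 0.75/86) = 0.5/0.187 = 2.68 on 83 df, critical value 1.989, power 0.75.

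| Correlation | Interaction, gradual | Interaction, sustained | ANCOVA at D6 |
|---|---|---|---|
| 0.3 | 0.39 | 0.51 | 0.67 |
| 0.5 | 0.53 | 0.66 | 0.75 |
| 0.7 | 0.76 | 0.88 | 0.89 |

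An effect present only at D6 has the same S as the sustained effect, and so the same interaction power.

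**4. Where the advantage ends.**

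- Compound symmetry, sustained effect, ρ = 0.8: both tests have power 0.97.
- AR(1), sustained effect, multivariate form of the interaction: 0.76 against 0.75 for ANCOVA at ρ = 0.7, and 0.91 against 0.85 at ρ = 0.8. The interaction is ahead. For a gradual effect ANCOVA stays ahead.
- Fading effect (0, 0.5, 0.25), ρ = 0.5: S = 0.125, so interaction power is again 0.53. ANCOVA at D6 has noncentrality 0.25/0.187 = 1.34 and power 0.26.

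**5. If only D3 and D6 are levels of time.** The interaction has 1 df and tests δ(D6) − δ(D3). For a benefit equal at both visits this is zero, so the test rejects only at its 5% error rate.

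**6. What 86 patients detect under a D6 primary analysis.** Solving the ANCOVA formula for δ at ρ = 0.3 / 0.5 / 0.7 gives 0.75 / 0.68 / 0.56 SD at 95% power, and 0.58 / 0.53 / 0.44 SD at 80% power.

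**The case against.** The defence has several sound points.

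- **Direction.** A reader might infer that the interaction is faulty because it would also be significant if RYJHS were worse. That does not hold: a two-sided D6 contrast has the same property, and the direction can be read from the means. What stands is that a 2-df test does not identify the visit.
- **Power.** A reader might infer that the interaction always loses power. It does not (step 4). At the planned f = 0.25 no material power is lost either: both tests exceed 0.95.
- **Transient effects.** A significant interaction driven by D3 alone would be a real treatment difference at a scheduled visit, not a false positive. The protocol does not say that D6 alone must decide, so choosing D6 is a recommendation. It rests on D6 being the end of the second course.
- **Baseline as a time level.** This is a strong inference from Outcome Measurements and Table 2, but it is not stated. The alternative reading (step 5) is no better.
- **Regression models.** A reader might infer that the plan has no adjusted treatment comparison at all. It has regression models, but they name no visit and do not state adjustment for baseline PRWE, so they do not settle which estimate decides.
- **Details left to an analysis plan.** A condensed article may omit a contrast or an interval, and those omissions alone would not be a finding. The interaction test is different, because the article fixes it.

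**Conclusion.** The point holds in a limited form. The test that the protocol fixes for its primary outcome does not answer by how much PRWE differs between arms after two courses. That holds at every correlation and for either reading of time.

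The power argument is secondary and conditional. Under compound symmetry with 0.5 SD at D6 and 86 evaluable patients, baseline-adjusted ANCOVA gains 13 to 28 percentage points for a gradual effect and 2 to 16 points for a sustained one, over correlations 0.3 to 0.7. It gains nothing for sustained effects near 0.8 and loses where the effect fades after D3.

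A reader might infer that the claimed 95% power is an error. It is not: 86 reproduces for the interaction at f = 0.25 under the assumptions in step 1. The difficulty is that f = 0.25 on an interaction corresponds to no stated PRWE benefit. The trial remains valid; the change should be made so that its main result can be read as efficacy.

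**What to change.** Before unblinding:

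1. Make the primary analysis the RYJHS-minus-placebo difference in PRWE at D6, two-sided 5%, with a 95% CI. Obtain it from a mixed model on D3 and D6 with baseline PRWE as covariate and visit-by-treatment terms, or from ANCOVA at D6.
2. Report the D3 difference as secondary, and keep the interaction test as supportive.
3. In Sample Size Calculation, state that 86 was derived for the interaction, and give the D6 difference it detects under the new primary analysis with the assumed correlation (for example 0.68 SD at 95% power if the correlation is 0.5).

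**Cost:** revised analysis wording and a restated sample-size justification. No new data and no change in enrolment are needed. The real downside is lower power for an effect present mainly at D3.

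### The named primary analysis, repeated-measures ANOVA, keeps only patients with all three PRWE scores, so the comparison could be biased if loss relates to earlier PRWE differently in the two arms

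*Protocol article*

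**What the plan says.** Statistical Analysis names the method for wrist function: "We will use repeated-measures ANOVA to determine if changes in wrist function" come from the interaction of treatment type and measurement time. The software is SPSS version 22; no procedure within it is named. Sample Size Calculation uses the same test, "repeated-measures ANOVA within-between interactions with a medium effect size of f=0.25 and α level=.05", and continues: "To achieve a statistical power of 0.95, we calculated a total sample size of 86". The margin above that is explained in one sentence: "To account for potential dropouts and satisfy our inclusion criteria, we will enroll 100 individuals". No dropout rate or number is given.

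Outcome Measurements fixes the endpoint ("The primary outcome is the PRWE score, which is used to assess wrist function recovery") and the times: "data will be collected before the trial, as well as 3 days and 6 days after topical medication application". Table 2 places PRWE at baseline, D3 and D6, and labels D6 as the at-home treatment. Study Settings and Participants agrees: the first course takes place in hospital, with "the second course completed 3 days after discharge". Ethical Considerations lets participants withdraw at any time. The limitations paragraph of the Discussion concedes that use of the patch on schedule after discharge may be hard to confirm.

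**The concern.** The trial is both sized on and analysed by the within-between interaction of a repeated-measures ANOVA, so the term means the classical procedure and is not loose wording for a mixed model. That procedure works on complete vectors. In SPSS it is GLM Repeated Measures, which deletes listwise. A patient with baseline and D3 scores but no D6 score contributes nothing.

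Two things follow. The analysed set is no longer everyone randomised. And the comparison is among completers, which is safe only if the reasons for leaving, as far as they relate to PRWE, act alike in both arms. An active patch and a placebo patch may differ in skin reactions or early relief, so that cannot be taken for granted. The application site is monitored with the DASI score for exactly such reactions.

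**Working it through.** **1. The plan's own figure.** Inputs from Sample Size Calculation: f = 0.25, α = .05, power 0.95, interaction test. Inputs from the design: 2 groups and m = 3 measurements. The correlation among measurements is not stated; ρ = 0 is assumed because it reproduces the result. With λ = f²·N·m/(1 − ρ):

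- Multivariate form, df 2 and N − 3. At N = 86, λ = 0.0625 × 86 × 3 = 16.125 and power is 0.951. At N = 84 power is 0.946. So N = 86, as stated.
- Univariate form, df 2 and 2(N − 2). N = 84 gives power 0.9503.

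**2. The margin.** 100 − 86 = 14, and 86/(1 − 0.14) = 100. Fourteen is an allowance obtained by subtraction.

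**3. Power after losses (univariate, ρ = 0).** 100 complete patients: 0.978. 86: 0.955. 80: 0.940. 70: 0.904. Fourteen losses leave the planned power intact.

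**4. Bias.** The documents give no correlations and no attrition data, so everything here is an assumption: 50 per arm; SD 1; correlations .4 (baseline-D3), .2 (baseline-D6) and .7 (D3-D6); 12-15% loss at D6 by a logistic model on the D3 score; true D6 effect 0.50 SD. The quantity compared is the between-arm difference in change from baseline to D6, which is one component of the interaction.

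| How D6 loss depends on D3 | Complete-case change | Likelihood, all data |
|---|---|---|
| Opposite directions in the two arms | about 0.41 | 0.50 |
| One arm only | about 0.46 | 0.50 |
| Same in both arms | 0.49 to 0.51 | 0.50 |
| Random | no bias | 0.50 |

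The reason is simple. Change to D6 has regression slope .7 − .4 = .3 on the D3 score, so a D3 imbalance created by selective loss carries through at 0.3 of its size. If the D3 score is equally correlated with baseline and D6, the slope is zero and this mechanism produces no bias. That was confirmed with all correlations at .5. With .5/.3/.7 and opposite mechanisms, the estimate is 0.44.

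A harsher mechanism can push the other way. Suppose the 7 patients per arm with the worst change from baseline to D3 are lost, with correlations .7/.49/.7 and a true effect of −0.50. Complete-case change is then −0.66 if this holds in the treated arm only (loss random in control), and −0.83 if the control arm instead loses its best changers. Likelihood gives −0.50 in both cases, and with the same mechanism in both arms neither method is biased.

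**5. Precision.** The change-score variance is 2(1 − .2) = 1.6.

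- Change score, no missing data: SE = √(1.6 × 2/50) = 0.25.
- Change score, 43 per arm: √(1.6 × 2/43) = 0.27.
- Baseline-adjusted, 43 per arm: √((1 − .2²) × 2/43) = 0.21.
- Likelihood estimate, all data (simulated): 0.21.

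Missing data move the change-score SE from about 0.25 to 0.27. The further step to 0.21 comes from adjusting for baseline.

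**The case against.** The strongest reply is that missing-data handling and the analysis set are commonly left to a statistical analysis plan, which is not shown, and that this article condenses a fuller protocol. That is right as far as it goes: silence on imputation is no fault here, and imputation before ANOVA is not ruled out. But the article does fix a primary method, and the sample size rests on the same one. Moving to a mixed model would replace that method. The point is therefore about a stated choice.

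The reply also limits the size of the point, and these parts stand:

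- A reader might infer that the plan expects 14 of 100 patients to drop out. It does not. It speaks of potential dropouts, gives no number, and ties the margin to the inclusion criteria as well.
- A reader might infer that the trial would be underpowered. Fourteen losses leave the calculated 86.
- A reader might infer that the comparison will be biased. Bias needs arm-specific dependence on earlier scores. The trial is double-blind, and nothing in the documents shows such dependence. In the milder illustration the bias is 0.04 to 0.09 SD, at most about a third of one standard error.
- A reader might credit the mixed model with a large precision gain from rescued data. Most of that gain is baseline adjustment, which complete cases could also have.
- That losses concentrate at D6 is inferred from the schedule. Follow-up is only six days and losses may be few.

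**Conclusion.** The concern holds in a limited form. As named, the primary analysis is a complete-case analysis that discards partly observed patients, in a trial whose plan allows for dropouts and takes its last PRWE score after discharge. The consequence is a possible bias, of either sign. It is nil if loss is random or works alike in both arms. Under the milder assumptions it takes a true 0.50 SD to about 0.46 or 0.41; under deliberately harsh ones it takes a true −0.50 SD to −0.66 or −0.83. All of these rest on assumed correlations and loss mechanisms. The documents support neither a forecast of 14 dropouts nor a loss of planned power, and the loss of precision from missing scores alone is small. The change is worth making because it removes the risk in cases where loss depends on scores already recorded, at almost no cost.

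**What to change.** Before unblinding, make the primary analysis a likelihood-based mixed model for repeated measures (MIXED in SPSS): D3 and D6 PRWE as outcomes; treatment, time and treatment-by-time as fixed effects; baseline PRWE as covariate; unstructured covariance. Include every randomised patient with any post-baseline PRWE score, analysed as randomised. Keep the complete-case repeated-measures ANOVA as a sensitivity analysis.

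The cost is a change of analysis wording. The software, visits and enrolment target are unaffected. Two limits should be stated with it. The model assumes loss is missing at random, so it does not protect against patients who skip D6 because of how they are on that day. It also leaves out anyone with no post-baseline score.
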